**THESE REPORTING REQUIREMENTS APPLY TO EVERYONE WORKING WITH CANCER CENTER INSTITUTIONAL PROTOCOLS.**

**What is considered an SAE under this mandatory procedure?**

Any **unexpected grade 4** event not including routinely experienced events per protocol (e.g. myelosuppression) and **all grade 5 events** (death during protocol intervention) should be reported. The patient is considered “on-treatment” as defined in the protocol, which can extend days/weeks/months past the last date of actual protocol intervention.

Top of Form

Bottom of Form

| **Table 1: Summary of STRC Reporting Requirements for Institutional Pilot, Phase 1, Phase 2 and Phase 3 Interventional Trials** | | | | | | |
| --- | --- | --- | --- | --- | --- | --- |
|  | **ADVERSE EVENT** | | | | | |
|  | **Grade 1, Grade 2, Grade 3** | | **Grade 4** | | **Grade 5** | |
|  | **Unexpected** | **Expected** | **Unexpected** | **Expected** | **Unexpected** | **Expected** |
| **Unrelated** | Not Required | Not Required | **REPORT TO STRC** | Not Required | **REPORT TO STRC** | **REPORT TO STRC** |
| **Unlikely** | Not Required | Not Required | **REPORT TO STRC** | Not Required | **REPORT TO STRC** | **REPORT TO STRC** |
| **Possible** | Not Required | Not Required | **REPORT TO STRC** | Not Required | **REPORT TO STRC** | **REPORT TO STRC** |
| **Probable** | Not Required | Not Required | **REPORT TO STRC** | Not Required | **REPORT TO STRC** | **REPORT TO STRC** |
| **Definite** | Not Required | Not Required | **REPORT TO STRC** | Not Required | **REPORT TO STRC** | **REPORT TO STRC** |

STRC reporting may not be appropriate for specific expected adverse events for protocols. In those situations the adverse events that will not require STRC reporting **must be specified in the text of the approved protocol.**

**STRC notification responsibilities of the person handling the reporting/documenting of the SAE:**

1. Make a phone call to the appropriate clinical member of the STRC as listed below (page if necessary)—see note 2 below
2. Submit the STRC Notification Form WITHIN 24 HOURS of first knowledge of the event. This form is found at either the ORIS main menu page or by going to <http://ccc.wfubmc.edu/oris/strc.aspx>.

This will ensure that all persons that the event applies to will be notified; remember to file a copy of your confirmation. (Form instructions will walk you through the required fields, consult the help page for further instructions.)

1. Ensure that you document that the appropriate persons on the STRC has been contacted.
2. Follow up with/update the clinical member of STRC regarding any new developments or information obtained during the course of the SAE investigation and reporting process.

**Elements needed to complete the electronic STRC form:**

1. ORIS Patient ID (PID)
2. Name of STRC Clinician notified/Date/Time/Comments.
3. Grade of event.
4. Is this related to protocol intervention or treatment?
5. Is suspension of the protocol needed?
6. Is any change to consent or protocol needed?
7. Was the nature or severity of the event unexpected?
8. Date of the event.
9. Brief description of the event using approved CTC version terminology.
10. Date of last study dose before event.
11. Relevant tests/labs.
12. **Most importantly make sure that the Investigator assigns attribution to the reported event (grade) using the appropriate CTCAE version for the protocol.**

**STRC CLINICAN RESPONSIBILITY:**

It is the responsibility of the STRC clinician to review all reported events, evaluate the events as they are reported; and communicate a response to the Investigator, event reporter and the members of STRC. The review will include but not be limited to the information reported; there may be times when additional information is needed in order for an assessment to be made further communication directly with the investigator may be warranted. STRC reserves the right to agree with the investigator’s assessment if STRC does not agree with the investigator STRC reserves the right to suspend the trial pending further investigation.

**AMENDMENTS TO PREVIOUS REPORTS**

If you are not able to supply all pertinent information with the initial submission, once the additional information is available **do not submit a new report**. Go to the original email that was received by STRC and others “reply to all” and entitle your email “**Amendment** for (list date of event and patient ID) this will avoid duplications of the same event. List the additional information which you are reporting.

| **Adverse Event Description** | **Cycle of Toxicity Onset** | **Start Date** | **Stop Date** | **AE Type** | **Grade (1-5)**  **per CTC v. 4.0** | **Attribution** | **Serious** | **Action Taken** | **MD initials / date** |
| --- | --- | --- | --- | --- | --- | --- | --- | --- | --- |
|  |  |  |  | 🞎Expected  🞎Unexpected | 🞎Mild/1  🞎Moderate/2  🞎Severe/3  🞎Life- threatening/4  🞎Death/5 | 🞎Related  🞎Probably  🞎Possible  🞎Unlikely  🞎Unrelated | 🞎No  🞎Hospitalization  🞎Disability  🞎Birth Defect  🞎Life-threatening  🞎Death  🞎Other: _______ | 🞎None  🞎Therapy Withheld  🞎Therapy D/C  🞎Therapy Adjusted  🞎Other: _______  🞎N/A |  |
|  |  |  |  | 🞎Expected  🞎Unexpected | 🞎Mild/1  🞎Moderate/2  🞎Severe/3  🞎Life- threatening/4  🞎Death/5 | 🞎Related  🞎Probably  🞎Possible  🞎Unlikely  🞎Unrelated | 🞎No  🞎Hospitalization  🞎Disability  🞎Birth Defect  🞎Life-threatening  🞎Death  🞎Other: _______ | 🞎None  🞎Therapy Withheld  🞎Therapy D/C  🞎Therapy Adjusted  🞎Other: _______  🞎N/A |  |
|  |  |  |  | 🞎Expected  🞎Unexpected | 🞎Mild/1  🞎Moderate/2  🞎Severe/3  🞎Life- threatening/4  🞎Death/5 | 🞎Related  🞎Probably  🞎Possible  🞎Unlikely  🞎Unrelated | 🞎No  🞎Hospitalization  🞎Disability  🞎Birth Defect  🞎Life-threatening  🞎Death  🞎Other: _______ | 🞎None  🞎Therapy Withheld  🞎Therapy D/C  🞎Therapy Adjusted  🞎Other: _______  🞎N/A |  |
|  |  |  |  | 🞎Expected  🞎Unexpected | 🞎Mild/1  🞎Moderate/2  🞎Severe/3  🞎Life- threatening/4  🞎Death/5 | 🞎Related  🞎Probably  🞎Possible  🞎Unlikely  🞎Unrelated | 🞎No  🞎Hospitalization  🞎Disability  🞎Birth Defect  🞎Life-threatening  🞎Death  🞎Other: _______ | 🞎None  🞎Therapy Withheld  🞎Therapy D/C  🞎Therapy Adjusted  🞎Other: _______  🞎N/A |  |

# APPENDIX C – CCCWFU ADVERSE EVENT LOG

# *Only Grade 3 OR higher Need to be recorded*

# APPENDIX D – Data Collection Form for Efficacy Assessment

**ORIS PID:** _______________________ **Date Completed:** ____ / ____ / ____

**Visit:**  Pre-study  Cycle 1 Visit  Cycle 2 Visit  Cycle 3 Visit  Cycle 4 Visit

Cycle 5 Visit  Cycle 6 Visit  Cycle 7 Visit  Cycle 8 Visit  Cycle 9 Visit

Cycle 10 Visit  Other (Specify: _________________________________)

**ECOG Performance Status (Date Performed:** ____ / ____ / ____)

0 Fully active, able to carry on all pre-disease performance without restriction.

1 Restricted in physically strenuous activity but ambulatory and able to carry out work of a light or sedentary nature, e.g., light house work, office work.

2 Ambulatory and capable of all self-care but unable to carry out any work activities. Up and about more than 50% of waking hours.

3 Capable of only limited self-care. Confined to bed or chair more than 50% of waking hours.

4 Completely disabled. Cannot carry on any self-care. Totally confined to bed or chair.

**Date of contrast CT (chest / abdomen) and/or PET/CT**: ____ / ____ / ____

**Were new lesions identified on contrast CT (chest / abdomen) and/or PET/CT?**  Yes  No

**Has this subject progressed according to RECIST criteria? (As determined by the treating physician)**  Yes  No

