| * Cycle Length is 4 weeks, with treatment on Days 1 and 4 of Weeks 1 through 3; week 4 is a rest  week (no treatment)  ** The only pre-study data that will be used for data analyses are ECOG status, baseline CT or PET/CT, and LDH. See section 5.1.4 for details.  a: Pre-study requirements must be completed **within** **the following time**  **frames:**  Within **4** weeks: tumor assessments based on contrast CT of chest and abdomen or PET/CT;  Within **2** weeks: medical history, physical exam, vital signs, height, weight, ECOG, evaluation of symptoms and medications, clinical chemistry, hematology, LDH  Within **1** week: pregnancy test for women of childbearing potential  b: Specific chemistries are listed in section 5.2.2. Renal function will be assessed using the Cockcroft-Gault formula.  c: Serum pregnancy test for women of childbearing potential  d: These tests are performed with results available for review within 24 hours before administration of CPI-613  e: CPI-613 is given as a 2-hr IV infusion via a central venous catheter. Treatment with CPI-613 may be adjusted +/- 1 day.  f: Imaging performed while on treatment should be preferably obtained on day 3, 4, or 5 of week 4 during cycles 2, 4,  6 and every two cycles thereafter until progression.  g: Survival and post-study cancer treatment will be monitored bimonthly via telephone contact by the study PA after  patients are taken off of the trial. Phone contact will continue indefinitely.  h: Physical exam and clinical evaluation to be completed within 72 hours prior to treatment with CPI-613 | | | | | | | | | |

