### 5.1.2 Safety Assessment

The safety of CPI-613 will be assessed from the first dose to 1 month after last dose of CPI-613. The assessment will be based on:

- evaluation of symptoms

- vital signs

- ECOG performance status and survival

- clinical chemistry

- renal function

- hematology

The specifics of the safety tests are described in Section 5.2. All safety assessment tests are performed during screening (performed within 2 weeks prior to Cycle 1 treatment with CPI-613. Symptom evaluation and vital signs should be performed prior to each administration of CPI-613. ECOG performance status, clinical chemistries, renal function, and hematology should be performed on day 1 of weeks 1, 2, and 3 for each treatment cycle, with results available for review within 24 hours before administration on day 1 of study drug administration.

###

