## 6.2 Adverse Event-Related Dosing Delay and Dose Modification

For adverse events unrelated to serum creatinine elevation or reduction in renal function but are possibly related to CPI-613, the occurrence of Grade 1 toxicity does not generally require dose modification for subsequent doses for that patient. However, if Grade 2 toxicity (other than alopecia and nausea) probably related to CPI-613 develops, treatment is to be withheld and can resume only after the Grade 2 toxicity has been reduced to Grade 1 or below, and the dose level for subsequent doses for that patient will be reduced by 25% of the dose at which such Grade 2 toxicity occurs. Grade 2 alopecia and nausea do not require withholding treatment or dose reduction. If Grade 3 or 4 toxicity probably related to CPI-613 develops, dosing of CPI-613 of that patient will be withheld and the patient shall be monitored for recovery from, and reversibility of, such Grade 3 or 4 toxicity. To resume treatment with CPI-613 for a patient who has had CPI-613-related Grade 3 or 4 toxicity, the Grade 3 or 4 toxicity must be reduced to Grade 1 or below, and the dose level for subsequent doses for that patient will be reduced to 50% of the dose at which such Grade 3 or 4 toxicity occurs.

For adverse events related to creatinine elevation or reduction in renal function that are possibly related to CPI-613, dosing of the patient will be withheld if the severity level is Grade 1 or above. Treatment can resume only after the toxicity has been reduced to Grade 0. The dose level for subsequent doses for that patient will be reduced by 15% if the severity level is of Grade 1, by 25% for Grade 2 toxicity, and by 50% for Grade 3 or 4 toxicity.

Furthermore, if the toxicity possibly related to CPI-613 is acute renal failure and the severity level is Grade 3 or 4, further patient enrollment will be temporarily suspended in order to enable assessment of the following aspects of the trial and implementation of corrective measures or protocol amendment, and if necessary:

- compliance of the study sites and investigators to the study protocol

- evaluation of the appropriateness of the procedures for monitoring renal function

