**List of Adverse Events to be Reported:**

*Abdominal pain

*Alkaline phosphatase

*ALT (SGPT)

*Anorexia

*AST (SGOT)

*Bilirubin (hyperbilirubinemia)

*Calcium (hypercalcemia, hypocalcemia)

*Creatinine

*Diarrhea

*Flushing

*Hemoglobin (anemia)

*Injection site Reaction

*Leukocytes

*Lymphopenia

*Nausea

*Neutrophils (neutropenia)

*Platelets (thrombocytopenia)

*Potassium

*Sodium

*Vomiting

All adverse events should be reported in the AE reporting log (Appendix C) and in ORIS regardless of whether they are on this list. Asterisk (*) denotes expected Adverse Events.

All Serious Adverse Events (SAEs) which are Possibly, Probably or Definitively Related to CPI-613, and Unexpected are required to be reported to Cornerstone Pharmaceuticals via the provided SAE Reporting Form within 7 days. All completed forms must be sent to [name] at Cornerstone. Cornerstone will submit any applicable SAEs to the FDA.

SAE reports must be submitted to Cornerstone by fax or email to the following address:

Department of Regulatory and Clinical Affairs

Cornerstone Pharmaceuticals, Inc.

[name]

[name]

[contact]

Telefax: [contact]

Email: [[contact]](mailto:[contact])

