# 9.0 STATISTICAL CONSIDERATIONS

This is a pilot study with the primary goal to be able to determine initial estimates of response rate (RR), and secondary goals to determine progression-free survival (PFS) and overall survival (OS). Data from this trial will also provide additional data concerning the safety profile of the CPI-613 therapy. We now describe anticipated accrual rates, proposed analyses, and sample size considerations.

Accrual Rate

We anticipate accruing one to two patients per month for this protocol. Thus, we anticipate that we will reach the target sample size of 20 patients treated at MTD within eighteen months.

Proposed Analyses

The analyses for this protocol will be primarily descriptive. With a sample size of 20 treated at MTD, we will be able to get initial estimates of RR, PFS, OS, and safety and toxicity.

For the primary outcome of tumor response rate we will present the proportion of patients who are CR, PR, SD or PD (Complete response, Partial response, stable disease and progressive disease, respectively). In addition, we will estimate the proportion of responders as the percent of patients who are SD, PR and CR, as well as RR (sum of PR + CR) and Disease Control Rate (DCR, which is the sum of SD, PR and CR). For these rates we will also include 95% confidence intervals.

For the time-to-event outcomes, we will estimate survival curves for OS and PFS using Kaplan-Meier techniques. In addition, we will estimate the 6 month and 1-year OS and PFS rates for these participants. We will estimate median overall and progression free survivals for these patients as well. We will also examine safety and toxicities for these 20 patients by looking at each toxicity identified earlier in the protocol by grade.

Sample Size Considerations

Since this is a single arm pilot study, our primary goal is to gather preliminary data on response rates and not to test a specific hypothesis per se. With this sample size we will be able to estimate the response rate using a 2-sided 95% confidence interval with an interval that will extend no more than 0.21 from the observed response rate (if we conservatively assume a response rate of 0.5 for calculations).

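### The Appendix C log asks only for Grade 3 or higher, while Section 8.1 wants all adverse events and Section 9.0 tabulates by grade, so Grade 1–2 toxicity may be under-recorded

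*Protocol*

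**What the plan says.** The instruction in the body of the protocol is in Section 8.1, under the list of adverse events: "All adverse events should be reported in the AE reporting log (Appendix C) and in ORIS regardless of whether they are on this list". It gives no grade limit. The list has 20 toxicities.

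Appendix C is the log that this sentence names. Its heading reads "Only Grade 3 OR higher Need to be recorded". The form has a grade column running from 1 to 5 with separate boxes for mild and moderate events, and an action-taken column with options for therapy withheld and therapy adjusted.

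Section 9.0 states that with 20 patients "we will be able to get initial estimates of RR, PFS, OS, and safety and toxicity", and that safety will be examined "by looking at each toxicity identified earlier in the protocol by grade". Safety and toxicity are secondary outcomes in Section 2.2.

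Section 6.2 links dosing to grades below 3: "if Grade 2 toxicity (other than alopecia and nausea) probably related to CPI-613 develops, treatment is to be withheld", with a dose reduction on resumption. For renal events possibly related to the drug, withholding and reduction begin at Grade 1.

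On timing, Section 5.1.2 states: "Symptom evaluation and vital signs should be performed prior to each administration of CPI-613". Table 5-1 marks on-treatment symptom evaluation on Week 1 Day 1 only.

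**The concern.** Two instructions govern the same log and cannot both be followed as worded. The one printed on the form is the one staff see when they fill it in. If they follow it, low-grade events are recorded unevenly or not at all, while the analysis in Section 9.0 assumes that every grade is available.

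The error would run one way. Omitted Grade 1–2 events can only lower the reported low-grade rates, so tolerability would look better than it was. Some of the omitted events could be the reason a dose was withheld or reduced under Section 6.2. Among the forms shown, the log's action-taken column is the only field that ties an adverse event to a dose action. An analysis plan written later cannot recover symptoms that were never written down.

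**Working it through.** The protocol gives no figure to reproduce here. The check sets the passages side by side and then counts what is exposed.

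**1. The instructions compared**

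| Place | Grades called for |
| --- | --- |
| Section 8.1, adverse event list | All, in the Appendix C log and in ORIS |
| Appendix C heading | Grade 3 or higher |
| Log form, grade column | Boxes for 1 to 5 |
| Section 9.0, Proposed Analyses | Each listed toxicity, by grade |
| Section 6.2, non-renal events | Dose action from Grade 2 (alopecia and nausea exempt at that grade) |
| Section 6.2, renal events | Dose action from Grade 1 |

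Only the Appendix C heading sets a threshold at Grade 3. All the other places either call for lower grades, provide for them or use them.

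**2. Size of the planned table**

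Taking the five grade boxes on the form, the nominal grid is 20 toxicities × 5 grades = 100 cells. Those below the heading's threshold are 20 × 2 = 40.

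**3. Which toxicities depend on the log**

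- Laboratory values (13): alkaline phosphatase, ALT, AST, bilirubin, calcium, creatinine, hemoglobin, leukocytes, lymphopenia, neutrophils, platelets, potassium, sodium. All are covered by the panels in Section 5.2.2, drawn on Day 1 of Weeks 1, 2 and 3 of each cycle.
- Symptom-type (7): abdominal pain, anorexia, diarrhea, flushing, injection site reaction, nausea, vomiting. No laboratory result can stand in for these.

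The 40 low-grade cells therefore split into 13 × 2 = 26 that could in principle be rebuilt from laboratory results and 7 × 2 = 14 that rest on someone recording the event.

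**4. Would there be low-grade events to miss?**

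The protocol states no low-grade rates, so I assume a range. With true rate p for a given toxicity in 20 patients, the chance of at least one case is 1 − (1 − p)^20 and the expected count is 20p.

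| Assumed Grade 1–2 rate | Chance of at least one case | Expected cases |
| --- | --- | --- |
| 10% | 0.878 | 2 |
| 20% | 0.988 | 4 |
| 30% | 0.999 | 6 |
| 50% | >0.999 | 10 |

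If a share q of these cases is left off, the log shows 20p(1 − q). At p = 30% the logged count can lie anywhere from 6 (q = 0, Section 8.1 followed) to 0 (q = 1, the heading followed throughout). The protocol does not allow q to be estimated.

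**5. Symptom evaluation schedule**

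There are six administrations per cycle (Days 1 and 4 of Weeks 1 to 3). Section 5.1.2 calls for symptom evaluation before all six. Table 5-1 marks one of the six, although it marks vital signs on all six.

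**The case against.** The strongest reply is that Section 8.1 already states the right rule and names a second destination. All events go to ORIS as well, and no grade limit is stated there. The log has boxes for Grades 1 and 2, and its heading can be read as a minimum, not a prohibition. Most of the listed toxicities are laboratory values drawn on schedule. This is also a descriptive 20-patient pilot whose primary outcome is response rate.

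Much of this stands, and it limits the consequence. It does not remove the contradiction. The fallbacks are also thinner than they look. The Section 10.0 table assigns ORIS only the consent document and the registration form, and lists no adverse event form. The data forms shown capture LDH but no other on-treatment chemistry or hematology. The symptom-type toxicities have no laboratory substitute.

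Several stronger readings are tempting but not supported:

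- *The by-grade table will be empty below Grade 3, with two grades lost for all 20 toxicities.* The ORIS route, the Grade 1–2 boxes and the 13 laboratory toxicities all argue against this.
- *Most dose holds will go unexplained.* The protocol gives no frequency of holds by grade, and Grade 3–4 events also trigger them.
- *Entry abnormalities cannot be separated from drug effects, because a Table 5-1 footnote says* "The only pre-study data that will be used for data analyses are ECOG status, baseline CT or PET/CT, and LDH". That footnote restricts pre-study data only. Chemistry, hematology and symptom evaluation are also scheduled on Week 1 Day 1, with results available for review in the 24 hours before dosing, so Cycle 1 provides a pre-dose baseline that the footnote does not exclude.
- *The Table 5-1 mismatch is itself shown data loss.* Section 5.1.2 still requires evaluation before each administration, and the log records start and stop dates, so events between visits can be captured.

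**Conclusion.** The protocol contradicts itself on which grades go in the Appendix C log, and the heading on the form is out of line with Sections 8.1, 9.0 and 6.2. The supportable consequence is that Grade 1–2 events, including some that trigger dose changes, may be missing or unevenly captured, with low-grade rates biased downward. At most 40 of the 100 nominal toxicity-by-grade cells are exposed, and 14 of them, for the 7 symptom-type toxicities, have no laboratory substitute. The actual loss depends on which instruction staff follow and on how fully ORIS is used, and neither can be judged from the protocol.

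This affects a secondary outcome and leaves the response-rate estimate untouched. It is still worth correcting before data are collected, because unlogged symptoms cannot be reliably reconstructed afterwards. The Table 5-1 and Section 5.1.2 mismatch is genuine but lesser.

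**What to change.** Replace the Appendix C heading with *All grades, all adverse events (Section 8.1)*, so that the log agrees with Section 8.1 and supplies what Section 9.0 needs. The cost is one form heading and modest extra data entry for 20 patients.

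If the Grade 3 limit is in fact intended, Sections 8.1 and 9.0 would have to be restricted to match. The protocol would also have to say where the lower-grade events used in Section 6.2 are recorded. That saves data entry but gives up the low-grade part of the planned safety description.

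Separately, reconcile the symptom-evaluation row of Table 5-1 with Section 5.1.2 so that both state the same timing. This is an edit to one table row or one sentence.
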